## Abstract

**Background:**

Frailty describes an age-related clinical state and can be regarded as a predictive factor for fall, disability, hospitalization, and death in the elderly. Previous studies proved that frailty could be reversed or attenuated by multi-disciplinary intervention. However, only a few studies have been performed in non-dialysis patients with chronic kidney disease.

**Methods:**

A randomized parallel controlled trial will be conducted to compare an individualized intervention according to the consequence of the comprehensive geriatric assessment with routine treatment. A total of 242 individuals aged ≥65 years, who fulfill the Fried Phenotype of frailty and have chronic kidney disease stage 3–5 without dialysis will be recruited from the Department of Nephrology and Department of Internal Medicine, Beijing Chaoyang Hospital, Capital Medical University. The participants will be followed-up for 30 days and 12 months.

**Discussion:**

This protocol would be established to examine the efficiency of targeted intervention for frailty. If a positive consequence could be obtained, a novel treatment for frail elderly patients with chronic kidney disease who have never undergone dialysis can be carried out in routine clinical practice.

**Trial registration:**

The trial was prospectively registered at the Chinese Clinical Trials Registry with the registration number ChiCTR-IOR-17013429 on November 17, 2017.

## Background

The accelerated speed of aging and the heterogeneity of elderly have led to an increasing focus on the frailty, which is recognized as an age-associated state of increased vulnerability to external stressors resulting from the decreased physiological reserve function of multiple systems [1, 2]. As a multidimensional concept involving physical, psychological, social, and environmental aspects [3], frailty is consistently believed to be associated with falls, disability, hospitalization, institutionalization, mortality, and other poor outcomes [4]. Although frailty is closely related to aging, it is not tantamount to aging and can be regarded as unsuccessful aging [5]. Occasionally, distinguishing frailty from comorbidity and disability is challenging; however, comorbidity is an etiological risk factor for frailty, while disability is an outcome of frailty [6] as postulated by gerontologists.

The knowledge about frailty aided in the development of various evaluation tools. Nevertheless, there is no consensus on the tools for measuring frailty. The most commonly used instrument is Frailty phenotype proposed by Fried et al. in 2001 [7]. Frailty is a common and pervasive condition among the elderly. According to the results of several studies, the prevalence of frailty in the community of elderly is up to 7–10% [8]. Notably, frailty increases with age, and females have a more pronounced statistical prevalence than males [8]. Despite the prevalence of frailty and its association with negative outcomes, it can be easily overlooked owing to the lack of the corresponding chief complaint or the manifestations encompassed by comorbidity [9]. Consequently, individuals ≥65 years should be routinely screened for frailty.

Several direct or indirect factors might be involved in the development of frailty, including low education level, depression, malnutrition, polypharmacy, low physical activity, and concomitant chronic disease [10]. The prevalence of comorbidity in frail individuals is higher than in those without frailty [4], among which, chronic kidney disease (CKD) is one of the most common diseases closely linked to frailty. Some studies found that the prevalence of frailty among patients with CKD or end-stage renal disBGR01491ease (ESRD) is 3-fold than that of patients without the disease [6]. Furthermore, frail patients undergoing hemodialysis were associated with a 2.6-fold higher risk of mortality and 1.43-fold higher risk of hospitalizations, independent of age, sex, comorbidity, and disability as compared to patients without frailty [11]. Among patients treated with peritoneal dialysis, the frail patient has a significantly high rate of death or hospitalization, as well as, prolonged duration of stay per admission [12]. Moreover, no significant difference was detected in frailty between patients with hemodialysis and peritoneal dialysis [13]. Similarly, after adjusting the recipient, donor, and other confounders, the risk of early hospital readmission and mortality of frailty patients after kidney transplantation were 1.61-fold and 2.17-fold, respectively, more than those who were non-frail [14, 15].

Several studies demonstrated that frailty could be reversed or attenuated by nutritional supplementation, cognitive training, psychological intervention, or physical exercise, and multi-domain interventions are superior to monodomain interventions, among which, exercise training plays an irreplaceable role [16]. Some investigators speculated that exercise training could ameliorate poor physical functioning and frailty. Moreover, the survival rate s in patients with CKD can be improved [17]. In the case of frail patients undergoing CKD, most investigations focus on those treated with dialysis. Currently, only a few studies have been performed in frail non-dialysis patients. Thus, the objectives of this clinical study are 1) to explore the risk factors related to frailty in elderly CKD patients without dialysis, 2) to investigate the effect of individualized interventions of frailty on the prognosis of elderly patients with CKD who did not undergo dialysis.

## Methods

### Design outline

A single center randomized parallel controlled trial with a follow-up period of 30 days and 12 months will be conducted. According to our pretest data, the reversion of frailty approached 25% in intervention group while 10% in control group, a total of 97 frail subjects are needed in each group (*α* = 0.05; *β* = 0.2; two-sided contrast). Considered a lost to follow-up rate of 20%, increased the sample size to 242. And, referring to relevant literatures, the frailty was reversed by individualized intervention, ratio is approaching 35 and 15% for the frailty versus non-frailty [16]. 71 patients for per group will be needed (*α* = 0.05; *β* = 0.2; two-sided contrast). Taking into account a rate of 20% loss to follow-up, increased the sample size to 178. Finally, the whole sample size is 242 in order to get the higher statistical power. All eligible participants will be randomized (1:1 allocation ratio) into control and intervention groups, and the latter would receive individualized interventions according to the consequence of the comprehensive geriatric assessment (CGA). The outcome data would be collected at baseline, 30 days, and 12 months (Fig. 1, Table 1).

**Fig. 1 Fig1:**
[figure not shown]
Schematic representation of the randomized controlled trial

[figure not shown]

**Table 1 Tab1:**
[figure not shown]
Schedule of the study

^a^It will be used as baseline data. ^b^Not applicable for everyone. *CKD-EPI* Chronic Kidney Disease Epidemiology Collaboration, *ADL* Activity of Daily Living, *IADL* Instrumental Activity of Daily Living, *MNA-SF* Mini-Nutritional Assessment Short Form, *GDS* Geriatric Depression Scale, *MMSE* Mini-Mental State Examination, *SPPB* Short Physical Performance Battery

The clinical study was supported by the Beijing Municipal Science and Technology Commission and the study protocol (Z171100000417055 V3.0) was reviewed and approved by the Medical Ethics Committee of Beijing Chaoyang Hospital, Capital Medical University, Beijing, China, and was approved unanimously (No. 2017-science-190). Participants will join in the clinical trial only after reading and signing the consent form. The right of participants to withdraw will be respected at any stage of the clinical trial. Deciding not to participate in the study will not affect usual medical care. Any collected data will be kept confidential. This study was registered as a randomized controlled clinical trial on 17 November 2017 (ChiCTR-IOR-17013429). Any change of the study scheme will be reported to the Medical Ethics Committee of Beijing Chaoyang Hospital, Capital Medical University and will be modified in the Chinese Clinical Trials Registry.

### Recruitment and eligibility

Eligible subjects will be identified and recruited in the Department of Nephrology and Department of Internal Medicine Beijing Chaoyang Hospital, Capital Medical University, including outpatients and inpatients. Recruitment will be conducted through printed materials (leaflets and posters). Patients will be required to fulfill the following criteria to qualify as study participants: 1) ≥65-years-old, 2) diagnosed as CKD stage 3–5, 3) never undergone hemodialysis or peritoneal dialysis, and 4) recognized as frailty by Fried scale. Chronic Kidney Disease Epidemiology Collaboration (CKD-EPI) formula is selected to estimate the glomerular filtration rate (eGFR); eGFR< 60 mL/min/1.73 m^2^ is defined as CKD stage 3–5 [18]. The informed consents will be signed after the eligible patients agree to participate in the investigation and allow access to their data during the follow-up either by clinic or telephone contact. Patients who are 1) undergoing dialysis, 2) considered with life expectancy < 1 year such as advanced cancer patients, 3) difficult to communicate with such as patients with severe cognitive impairment (Mini Mental State Examination score ≤ 17) [19]; or severe hearing disorder will be excluded from the study.

### Measurement and procedure

Frailty will be identified using Fried [20], including 5 components: 1) Shrinking, unintentional weight loss ≥10 pounds in last years or ≥ 5% of body weight in the previous year. 2) Weakness, based on grip strength, stratified by gender and body mass index (BMI) quartiles. For men, BMI ≤24 kg/m^2^, grip strength ≤29 kg; BMI 24.1–26 kg/m^2^, grip strength ≤30 kg; BMI 26.1–28 kg/m^2^, grip strength ≤30 kg; BMI > 28 kg/m^2^, grip strength ≤32 kg. For women, BMI ≤23 kg/m^2^, grip strength ≤17 kg; BMI 23.1–26 kg/m^2^, grip strength ≤17.3 kg; BMI 26.1–29 kg/m^2^, grip strength ≤18 kg; BMI > 29 kg/m^2^, grip strength ≤21 kg. In this study, we will measure the grip strength of the dominant hand twice to obtain the average. 3) Exhaustion, self-reported fatigue ≥3 days in the last week. 4) Low activity level, energy expenditure of physical activity per week < 383 kcal for men or < 270 kcal for women. 5) Slow gait speed, based on the time required for walking 15 ft. Walk time ≥ 7 s for men with ≤173 cm height or women with ≤159 cm height or walk time ≥ 6 s for men whose height was > 173 cm or women whose height was > 159 cm was considered as slowness. The presence of ≥3 criteria is defined as frailty, 1 or 2 is classified as pre-frailty, and 0 is regarded as non-frailty.

Frail elderly participants identified from candidates by Fried scale will receive CGA, containing activity of daily living (ADL) and instrumental activity of daily living (IADL) [21], mini-nutritional assessment short form (MNA-SF) [22], geriatric depression scale (GDS) [23], mini-mental state examination (MMSE) [19], and short physical performance battery (SPPB) [24]. ADL and IADL are designed to evaluate the basic self-care and necessary activities to run a household. The former includes eating, dressing, toileting, bathing, walking, and defecating, while the latter includes cooking, washing clothes, shopping, calling up, riding transportation, doing housework, managing money, and taking medicines. The dependence on performing ADL or IADL or both will be considered a disability. MNA-SF is a screening instrument to assess the nutrition status comprising of food intake, weight loss, mobility, disease acuity, BMI, and cognitive ability. As a result, scores ranging from 12 to 14, 8–11, and 0–7 represent normal nutrition status, the risk of malnutrition, and malnutrition, respectively. The GDS is often used to detect the depressive symptoms, which comprise of 30 items according to the common topical concerns of the elderly. A score of 0–9 indicates normal or absence of depressive symptoms, 10–30 indicates depression, of which, 10–19 means mild depressive symptoms, whereas 20–30 represents severe depressive symptoms. The MMSE is an instrument to identify the cognitive impairment including 30 questions encompassing 5 aspects of temporal and spatial orientation, memory, attention and calculation, recall ability, and language. Scores of MMSE < 24 indicate cognitive impairment. SPPB is a battery of objective physical performance including three tests of balance, sit-up for five times, and walking speed. The scores range from 0 to 12, and high scores denote superior function of lower extremity [25]. In addition to CGA, demographic information, lifestyle, and clinical profile of participants will be collected based on the gender, age, height, weight, education level, health care type, smoking and alcohol status, chronic comorbidities, echocardiography and laboratory variables.

All subjects who are involved in this study will be categorized into control and intervention groups based on a random number generated by the computer according to the ratio of 1:1 in a blinded manner. The information of random group allocation will be maintained in a sealed envelope opened only by a trial manager who is not involved in the recruitment, assessment, or intervention to assign the treatment. The control group will receive routine diagnosis and treatment, while the intervention group will receive individualized interventions in terms of the consequence of CGA based on routine diagnosis and treatment (Table 2).

**Table 2 Tab2:** Items of the intervention

Items	Intervention group		Control group
	Methods	Frequency	
Nutrition	Diet recommendation with/without nutritional supplementation	Throughout the trial	Routine treatment
Psychology	Psychotherapy with/without antidepressants	30 min, twice one week	
Physical function	Warm-up	30–45 min, three times one week	
	Walking forwards/backwards		
	Knee and hip extension		
	Static standing on one leg		
	Toe and heel raise		
	Knee lifts		
	Cool-down		

The intervention is not a fixed pattern, which will be performed and adjusted according to the frailty characteristics of participants assessed at baseline

The nutritionist will communicate with all participants to conduct a retrospective investigation on their diet and distribute a handbook to record their daily diet. For reference, the energy and protein/g of common food will be printed in the Handbook (Additional files 1 and 2). The patients of the intervention group with malnutrition or with the risk of malnutrition are recommended an optimal diet structure and daily intake of energy and protein. Nutritional preparations such as homogenate meal, whey protein powder, or enteral nutrition powder will be provided to the intervention group that requires additional supplementation according to the prescription of the nutritionist. Other individuals in the intervention and control groups were administered the same dose of artificial preparation consisting of maltodextrin, sugar, and water. All preparations will be seasoned with vanilla to mask the original flavor and placed in the same opaque bottle. The adherence of participants will be monitored every 2 weeks by phone contact.

The patients with depression, initially evaluated by GDS scale in intervention, would be further assessed by the psychologist and appropriate drugs administered to improve depression. In addition, depressive patients will receive one-to-one psychotherapy twice a week for 30 min each, including supportive psychotherapy, knowledge therapy, and behavioral relaxation therapy. Other enrolled individuals randomly assigned to the control group and assessed as not to be depressed in the intervention group would be guided to treat senescence and diseases in a correct way and be encouraged to socialize and embrace life with a positive attitude. The adherence of participants will be monitored every 2 weeks by phone contact.

The patients of the intervention group with poor physical function would receive exercise prescription tailored to the subjects’ physical ability from a trained specialist. The exercise training of moderate and gradually increasing intensity is home-based, three times a week, 30–45 min/session for 12 months, which aims at improving strength, balance, flexibility, and endurance of the elderly. The exercise will cover walking forwards/backwards, knee and hip extension, static standing on one leg, toe and heel raise, and knee lifts, which based on the literature and the American College of Sports Medicine recommendations for older adults [26, 27]. The emphasis of the training will be adjusted according to the physical performance tests of the participants. As the patient’s physical qualities increases, the training intensity will be gradually increased by increasing the repeated frequency of each action. In order to avoid exercise-related injuries, the corresponding warm-up and cool-down conducted before and after exercise training would be performed. All exercise training will be performed in the patient’s home. The specialist will contact the patients by phone every 2 weeks to monitor the execution of the exercise prescription and resolve the problems raised during training. If necessary, face-to-face guidance will be provided. For participants with normal physical performance in the intervention group and those in the control group, physical activities will be encouraged and a customized exercise program will not be prepared.

Participants with two or more problems will be treated simultaneously by the relevant specialists. Furthermore, the intervention group was subjected to the management of chronic disease and assessment of medication for rational use of medicine, which will be accomplished by geriatric doctors mainly. Discontinuation of the intervention may occur in case of health decline or if a participant wishes to stop taking part in the intervention group. Communication and encouragement will be used to improve adherence to intervention. Reasons and information for drop outs will be documented.

All participants will be followed up for 30 days and 12 months through clinic or telephone contact by specific personnel who are blinded to group allocation to minimize the bias. The content of follow-up will include frailty reassessment using frailty phenotype, frequency, time, main medical conditions of rehospitalization, death and echocardiography.

### Outcomes

Frailty is defined as the primary outcome to evaluate the efficiency of the personalized intervention treatment that reversed frailty to pre-frailty or non-frailty. The secondary outcomes are re-hospitalization and death that assess the effect of frailty on the prognosis of patients, medical examination such as echocardiography.

### Data collection and management

The questionnaires and functional tests will be performed face-to-face, among which, grip strength will be measured by electronic hand dynamometer (Takei Digital Grip Strength Dynamometer, Model T.K.K5401; Takei Scientific Instruments Co., Ltd., Niigata, Japan). Demographic information, concomitant diseases, echocardiography data and laboratory variables of participants will be collected from the data system of Beijing Chaoyang Hospital, Capital Medical University. The frequency, time, and main medical conditions of re-hospitalization will be obtained by telephone contact. All data will be collected by trained study personnel and stored on Microsoft Office Excel under the custody of specific staff. Quality of the entered data will be monitored by checking entry for a random sample of subjects prior to database locking. A data monitoring committee, responsible for data monitoring, interim analyses and auditing.

The study is ongoing. Follow-up visits will complete on September 2020. Statistical analysis and publication of the full results will take place until 2021.

### Statistical analysis

Participants’ demographic information, comorbidities, laboratory results, other clinical characteristics, frailty, consequences of the CGA, and outcomes at 30 days and 12 months will be presented by descriptive statistics. The measurement data in accordance with normal distribution would be described by mean values ± standard deviation, or else by median values and interquartile ranges. The enumeration data would be expressed as percentage or rate. The 95% confidence interval (CI) would be reported subsequently. To compare the differences between means, Student’s t-test will be performed, and the differences between frequencies will be compared by χ^2^ test or Fisher’s exact test. Logistic regression will be conducted to analyze the predictors of frailty and compare the groups with respect to dichotomous outcome variables. The odds ratios will represent the effect of predictors. Kaplan–Meier survival curve would be plotted, and the Cox proportional hazard regression model would assess the association between frailty and mortality. Missing data, due to loss to follow up, will be imputed using the last value carried forwards method [28]. Sensitivity analyses will be conducted to determine whether the results have been influenced by missing data. All data would be analyzed by SPSS version 23 (IBM Corp, Armonk, NY). *P*-values < 0.05 will be considered as statistically significant. All probabilities would be two-tailed.

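### Reversal of frailty is compared by an unadjusted frequency test and by logistic regression, with neither named primary and no stated use of the baseline Fried count, which sets how many criteria each participant must lose

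*Protocol article*

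**What the plan says.** All references are to the Methods of the protocol article.

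- **Entry** (Recruitment and eligibility): participants must be "recognized as frailty by Fried scale".
- **Classification** (Measurement and procedure): "The presence of ≥3 criteria is defined as frailty, 1 or 2 is classified as pre-frailty, and 0 is regarded as non-frailty". The scale has five components.
- **Primary outcome** (Outcomes): frailty, used to judge the "personalized intervention treatment that reversed frailty to pre-frailty or non-frailty". This is a yes/no outcome, met when the count falls to 2 or fewer.
- **Tests** (Statistical analysis): "the differences between frequencies will be compared by" a chi-square or Fisher's exact test. Separately, "Logistic regression will be conducted to analyze the predictors of frailty and compare the groups with respect to dichotomous outcome variables".

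The primary outcome fits both test statements. The section does not choose between them, and it does not mention the baseline Fried count as a covariate or stratifying factor.

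**The concern.** The baseline count is part of the arithmetic of the outcome. One participant counts as a success after shedding a single criterion, while another must shed three. A test that pools them without regard to the starting point treats this predictable variation as noise.

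Two things follow. First, some precision is given up, although the covariate is already in hand from the eligibility assessment. Second, if one arm happens to contain more people who enter with exactly 3 criteria, the unadjusted difference moves in that arm's favour, and nothing in the stated analysis corrects for it.

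Leaving the choice of test open adds to this. An unadjusted chi-square test and an adjusted logistic model can fall on opposite sides of 0.05 in the same data. The choice should not be open once the results can be seen.

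**Working it through.** **1. Required loss by starting count.** Reversal means 2 or fewer criteria.

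| Criteria at entry | Net loss needed |
|---|---|
| 3 | 3 − 2 = 1 |
| 4 | 4 − 2 = 2 |
| 5 | 5 − 2 = 3 |

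**2. The plan's own sample size** (Design outline: 25% vs 10%, two-sided α = 0.05, β = 0.2). With the unadjusted two-proportion formula and unpooled variance:

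n = (1.960 + 0.842)² × (0.25×0.75 + 0.10×0.90) / 0.15² = 96.8, so 97 per group, as stated. Allowing for 20% loss, 194 / 0.8 = 242.5, against the stated 242. The sample size therefore rests on an unadjusted comparison.

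**3. Power with and without the baseline count.** The article gives neither the distribution of counts nor reversal rates by count, so these are assumptions:

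- shares entering with 3/4/5 criteria: 60/30/10% or 45/35/20%;
- odds of reversal divided by 1 (no effect), 2.0, 3.3 or 7.4 for each extra criterion;
- overall reversal rates held at 25% and 10%.

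Each scenario was simulated 4,000 times. The chi-square test was compared with a likelihood-ratio test for arm in a logistic model containing arm and the count as a linear term.

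| Shares 3/4/5 | Odds factor | Power at 97 per group: unadjusted → adjusted | Gain (points) | Power at 121 per group: unadjusted → adjusted |
|---|---|---|---|---|
| 60/30/10 | 1 | 80.6 → 80.7% | 0.1 | 88.1 → 88.1% |
| 60/30/10 | 2.0 | 80.0 → 81.5% | 1.5 | 87.7 → 88.4% |
| 60/30/10 | 3.3 | 81.0 → 83.2% | 2.2 | 89.2 → 90.2% |
| 60/30/10 | 7.4 | 79.8 → 83.2% | 3.4 | 88.0 → 90.8% |
| 45/35/20 | 1 | 79.4 → 79.6% | 0.2 | 89.0 → 89.0% |
| 45/35/20 | 2.0 | 80.8 → 82.2% | 1.4 | 89.2 → 90.0% |
| 45/35/20 | 3.3 | 80.8 → 84.2% | 3.4 | 88.8 → 90.8% |
| 45/35/20 | 7.4 | 80.6 → 86.2% | 5.6 | 88.7 → 92.5% |

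With no treatment effect and 97 per group, the rejection rate was 4.7-5.5% for the chi-square test and 4.8-5.7% for the adjusted test (simulation error about 0.3 points). Both hold their level.

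**4. Chance imbalance.** With 121 per arm, the SD of the between-arm difference in the share entering with exactly 3 criteria is √(2×0.6×0.4/121) = 6.3 points, or √(2×0.45×0.55/121) = 6.4 points.

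Suppose a 2-SD imbalance is split equally, so that the intervention arm has 1 SD fewer such people and the control arm 1 SD more. The expected difference then falls by

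SD × [(rate at 3 − rate at 4-5, intervention) + (rate at 3 − rate at 4-5, control)].

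For 60/30/10% and a factor of 3.3: 6.3 × [(0.342 − 0.113) + (0.141 − 0.039)] = 2.1 points. Across both sets of shares the shift is 1.4-1.6 points (factor 2.0), 2.1-2.6 (factor 3.3) and 2.9-3.6 (factor 7.4), against a planned difference of 15. An imbalance of this size or more, in either direction, is roughly a 1-in-20 event.

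**The case against.** The strongest reply is that nothing stated is wrong. In a 1:1 randomised trial the unadjusted test is valid, its error rate already allows for chance imbalance, and it matches the basis of the sample size. Whether to adjust is a legitimate design choice. The gain is modest, depends on figures the article does not give, and vanishes if the count is not prognostic. All of this stands, and it makes the point an improvement in efficiency and pre-specification.

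It is also fair that an article condenses the plan and that the covariates of a logistic model often sit in the SAP, which is not shown. A reader might infer that the trial ignores the baseline count altogether. That holds for the chi-square or Fisher route as described. For the logistic model, the article only leaves the covariates unnamed.

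Three further inferences are tempting and not supported:

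- **Echocardiography compared by t-test without its baseline value.** The t-test is assigned to means in general and is not tied to echocardiography.
- **Randomisation lacks stratification.** Allocation is described as "based on a random number generated by the computer according to the ratio of 1:1". Silence on stratification in a condensed article does not show that there is none.
- **The model should also carry age, eGFR and care setting.** Recruitment covers inpatients and outpatients, but care setting is not in the listed baseline data. At 97 per group about 97×0.25 + 97×0.10 = 34 events are expected, and a longer model was not tested here. The outcome definition itself supports only the baseline count.

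What survives is that two methods are printed for one primary contrast, and that neither is said to use a covariate built into the outcome.

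**Conclusion.** The point holds as a recommended improvement. The article offers two tests for the primary outcome without ranking them, and describes neither as using the baseline Fried count, although its own definitions make that count a very likely predictor of reversal.

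A reader might take this to mean that the planned test is biased or that the trial is underpowered. Neither follows: the chi-square test held its level in the simulations and gave about the planned 80% power at 97 per group. The cost of not adjusting is about 0 to 6 power points at 97 per group, and 0 to about 4 at 121. The upper end needs a very strong effect of the count. A 2-SD chance imbalance would also move the expected unadjusted difference by about 1.4 to 3.6 points if the odds factor is 2.0 or more. All these sizes rest on assumed shares and odds factors.

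**What to change.** Before unblinding, state one primary test of reversal: a logistic regression on arm and baseline Fried count (3, 4 or 5). State how the count enters. The linear term simulated above uses one coefficient and avoids near-empty cells among those entering with 5 criteria. Report the standardised (marginal) risk difference with its 95% CI beside the odds ratio, because the sample size is set on the difference in proportions. Keep the unadjusted chi-square test as a supportive analysis. If the SAP already specifies such a model, it is enough to confirm that it is primary.

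The cost is a change of wording and a little programming for the standardised difference. No new data are needed, because the count is established at entry, and the sample size can stay as it is. The power figures above are for the likelihood-ratio test of the arm effect. The interval for the risk difference was not simulated, so the plan should say that the model-based test decides significance if the two disagree at the margin.

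### The only survival model named takes frailty, not the randomised arm, as the exposure for death, although every participant is frail at entry

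*Protocol article*

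**What the plan says.** Four parts of the protocol article bear on this.

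- **Entry.** The abstract describes the 242 participants as people "who fulfill the Fried Phenotype of frailty and have chronic kidney disease stage 3–5 without dialysis". Recruitment and eligibility lists "recognized as frailty by Fried scale" as the fourth inclusion criterion. Measurement and procedure gives the scale: "The presence of ≥3 criteria is defined as frailty, 1 or 2 is classified as pre-frailty, and 0 is regarded as non-frailty". Only the top category is eligible.
- **Objective.** The second objective, at the end of the Background, is "to investigate the effect of individualized interventions of frailty on the prognosis of elderly patients with CKD who did not undergo dialysis".
- **Outcomes.** The secondary outcomes are tied to frailty rather than to treatment: "The secondary outcomes are re-hospitalization and death that assess the effect of frailty on the prognosis of patients".
- **Analysis.** Statistical analysis plans a Kaplan–Meier curve, with no grouping stated, and says that "the Cox proportional hazard regression model would assess the association between frailty and mortality". The same section plans chi-square or Fisher tests for frequencies, and logistic regression that compares the groups on dichotomous outcomes.

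Frailty is measured again after randomisation, at 30 days and 12 months: "The content of follow-up will include frailty reassessment using frailty phenotype".

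**The concern.** The exposure in the survival model is stated, and it does not fit the design. The trial randomises 1:1 so that a difference in prognosis can be attributed to the intervention. The one time-to-event model named sets that aside and asks how frailty relates to death in a cohort where everyone starts frail. The Outcomes section makes the same substitution, so this is not a slip in one sentence.

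An analyst who follows the text has two direct choices. Frailty at entry gives no contrast. Frailty at follow-up gives one, but a non-randomised one that depends on surviving to the visit. As a fixed covariate timed from randomisation, the second choice makes reversal look protective even when it has no effect, which is the direction the trial hopes to see.

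**Working it through.** **Baseline frailty.** By the eligibility criteria 242 of 242 participants are frail. A covariate with one value has zero variance, cancels from the Cox partial likelihood and has no estimable coefficient. The text describes follow-up of trial participants only, so there is no non-frail cohort to supply a contrast.

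**Follow-up frailty as a fixed covariate.** The inputs are:

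- From the article (Design outline): reversal in 25% of the intervention group and 10% of the control group, averaging (25 + 10)/2 = 17.5% under 1:1 allocation, so p = 0.175.
- From the article (Measurement and procedure): frailty is reassessed at day 30 and at 12 months.
- Assumed, because the article gives no figure: 12-month mortality of 5–20%, constant hazard, no effect of reversal or arm on death, and everyone else followed to 12 months.
- Not stated in the article, so varied: the date at which reversal is taken to occur, with mean r as a fraction of the year.

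Anyone who would have reversed but dies first is counted as frail. When mortality is low, nearly everyone contributes a full year and the death rates are approximately

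- reversed: λ(1 − r), because no death can occur before reversal;
- frail: λ[(1 − p) + p·r]/(1 − p), because early deaths among would-be reversers are added here.

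The ratio of reversed to frail is therefore (1 − r)(1 − p)/[(1 − p) + p·r]. The true ratio is 1.

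| Reversal dated | Mean r | Approximate ratio | Exact ratio, mortality 5–20% |
|---|---|---|---|
| Day 30 | 30/365 = 0.082 | 0.918 × 0.825 / (0.825 + 0.014) = 0.90 | 0.89–0.90 |
| Uniform, day 0 to 365 | 0.5 | 0.5 × 0.825 / (0.825 + 0.0875) = 0.45 | 0.45 |
| Uniform, day 30 to 365 | (0.082 + 1)/2 = 0.541 | 0.459 × 0.825 / (0.825 + 0.095) = 0.41 | 0.41 |
| Half at day 30, half at 12 months | 0.541 | 0.41 | 0.42–0.44 |
| 12 months | 1 | 0 | 0 (no deaths among the reversed) |

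The exact column uses the exponential survival function in place of the low-mortality approximation. A simulation with the arm-specific rates of 25% and 10% agrees: the hazard ratio for frail versus reversed was 1.09–1.13 with reversal at day 30 (inverse about 0.9) and 2.12–2.23 with reversal uniform over the year (inverse 0.45–0.47). On the same simulated data the ratio by randomised arm was 0.99–1.01. A landmark at day 30, with only later deaths counted, gives 1.00.

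**Precision of the model by arm.** Assume 121 per arm with no loss and 10% control mortality. Expected deaths are 121 × 0.10 + 121 × (1 − 0.90^HR): 18.3 at a hazard ratio of 0.5 and 20.7 at 0.7. With 1:1 allocation, power is Φ(|ln HR| × √events / 2 − 1.96).

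- HR 0.5: Φ(0.693 × 4.28/2 − 1.96) = Φ(−0.48) = 32%.
- HR 0.7: Φ(0.357 × 4.55/2 − 1.96) = Φ(−1.15) = 13%.

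**The case against.** The best case for the plan has four parts.

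1. **A randomised comparison of the clinical outcomes is already planned.** Logistic regression and chi-square or Fisher tests compare the groups on dichotomous outcomes, and death and re-hospitalisation can be treated that way. With fixed 12-month follow-up, risk by arm is a legitimate estimand. This stands. A reader might infer that objective 2 goes unanswered, or that the frailty hazard ratio will be the trial's prognosis result; the article supports neither, and it gives the Cox model no such rank.
2. **The model need not be undefined or biased.** A day-30 landmark, a time-varying status, or the number of criteria met at entry (3 to 5) could all be fitted without this survival-time bias, and the landmark fits the visit schedule. This also stands. But the article states none of them, and each remains a non-randomised association that does not estimate the intervention effect.
3. **Detail belongs in the analysis plan.** For the Kaplan–Meier grouping, the time origin and the covariate coding, this is fair; the curve may well be intended by arm. It does not cover the Cox exposure, which the article names, nor the wording of the Outcomes section.
4. **A mortality model by arm would have little power.** True, as shown above. That is a reason to interpret the estimate cautiously, not to use a different exposure.

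A reader might also infer that someone who dies before readmission will be scored as not re-hospitalised. The article gives no rule either way, so that is not established.

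**Conclusion.** The point holds as a moderate one. The stated exposure of the only named survival model is wrong for this design: at baseline it has no contrast, and at follow-up, used as a fixed covariate, it is biased towards a benefit of reversal. The apparent ratio under no effect is about 0.9, about 0.4 or zero, depending on how reversal is dated. No single value should be quoted as the size of the bias, because the article does not fix the dating and gives no mortality figure. The result barely changes across the assumed 5–20% mortality; the dating of reversal drives it.

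The consequence is limited. The comparison of frailty reversal by arm is untouched, and death and re-hospitalisation can still be compared by arm as yes/no outcomes. What is missing from the stated plan is a survival model that addresses the intervention.

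**What to change.** - **Statistical analysis.** Make the randomised arm the Kaplan–Meier grouping and the Cox covariate for time from randomisation to death, censored at last contact.
- **Outcomes.** Reword so that death and re-hospitalisation assess the effect of the intervention, matching objective 2.
- **Frailty and mortality.** If this question is kept, label it exploratory and non-randomised, and use a day-30 landmark (day-30 status, deaths after day 30 only) or a time-varying status.

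The cost is wording, with no change to visits or sample size. Dates of death are needed; the article lists time explicitly for re-hospitalisation but not for death, so confirm that they are recorded (the planned Kaplan–Meier curve needs them anyway). The downside is low precision for mortality at 242 participants, so report the hazard ratio with its confidence interval rather than rely on a significance test. Time to first admission or death would add events, but it is a new endpoint, not a rewording, and is optional.
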